### Study design

This intervention will take a quasi-experimental design approach with an experimental and control site. The project will involve pre- and post-intervention data collection with one comparison group to assess intervention effects.

The study will be conducted at level 4 and 5 hospitals, each hospital having high volume of clients and covering a sub-county, all with similar maternal, newborn and child health indicators. Five hospitals will be the implementation sites while 4 hospitals will be control sites in a step wedge approach. The implementation sites will be selected purposely. The control sites will receive the full intervention after 1 year when the first set of comparison with the intervention site has been completed.

The 5 experimental site hospitals will receive a set of interventions which include: refurbishing of new born units, installation of equipment such as incubators, respirators, Ambu bags, and radiators. Establishment of a tele-health platform to enable free flow of information amongst clinicians and obstetricians, establishment of a call center for follow up of patients, training of health care providers in neonatology, and creating awareness amongst the community will be key cross cutting interventions, implying they will benefit the intervention site as well as control site. The control sites will not receive the main intervention benefits (equipped specialized newborn units) until after 1 year of implementation in the experimental sites.

The project will undertake a baseline, mid-term and end-line surveys. The step wedge design which allows for the measurement of process, outcome and impact indicators within each site (at different time points) will be used. The design also allows a comparison between different combinations of the intervention components.

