### Primary outcome measure

Percentage reduction in newborn deaths in Bungoma County between October 2015 and December 2018. This will be measured by comparing the number of newborn deaths at the nine project facilities (in the period of implementation), with the number of deaths at the same facilities in the similar period before the intervention; converted to percentage and aggregated by facility.

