## Discussion

The innovation has four components supporting each other as follows;Operation of telehealth platform which is an innovative tool that supports teleconsultations between professional paediatricians and the clinical offices at different health facilities. The telehealth platform essentially provides solution to the challenge of inadequate professionals in the target area which currently has a single paeditrician serving a total population of approximately 1.7 Million people. It enables realtime consultations between the clinical officers and the paeditricians. In addition, it enables professionals in distant locatilities bridge the gap by providing required services. There are 5 professionals from Nairobi (a distance of approximately 500 Kilometers) serving the population in addition to the one resident professional. It works by having the clinical officers take images of newborns under stress and share the same alongside clinical notes with professionals for advice in realtime.Call centre enables the call centre attendants who are trained nurses to consult with mothers of newborns and offer advice aimed at shortening decision making to seek care. This handles the challenge of delayed decisions to seek medical care. The mothers will call the call centre and present any challenges they face with their newborns with an aim of getting advise to handle the danger signs that they may have noted with their newborns. This enables them to make decisions to seek required medical care on time. Community engagement involves sensitizing the community members especially mothers of newborns of improved facilities within their locality. In addition, the community members are trained on how to identify danger signs in newborns and take remedial action in good time. This approach reduces the delay in seeking care for the newborns when required. When the community is sensitized, it becomes proactive and make relatively good decisions concerning the health of their newborns.Measuring results (outputs and outcomes) will involve undertaking a baseline survey to establish benchmarks that will be used to gauge the success of the intervention. This survey will involve the community within the target area, clinicians in selected health facilities and administrators of the health facilities including the County government officials who are legally incharge of the health facilities in the region. Outputs and outcomes will be established through internal and external evaluations which will be conducted at midterm and endterm of the project intervention (see Table 1). These will consider the benchmarks established at baseline to establish change in the situation beased on the intervention. This evaluation will be exhaustive enough and objective to ensure that only results that can be attributed to the intervention will be included since there are many other efforts towards improving the helthcare of newborns in the target area.

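### The primary outcome is a before-after change pooled over all nine hospitals, so the planned control comparison is not connected to it and background change counts as project effect

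*Protocol article*

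**What the plan says.** **Primary outcome measure.** The outcome is the percentage reduction in newborn deaths between October 2015 and December 2018. The section also fixes how it is obtained: deaths at the nine project facilities during implementation are set against those before, "with the number of deaths at the same facilities in the similar period before the intervention". The result is turned into a percentage and aggregated by facility.

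**Study design.** The project is to use "pre- and post-intervention data collection with one comparison group to assess intervention effects". On allocation: "Five hospitals will be the implementation sites while 4 hospitals will be control sites in a step wedge approach". On timing: "The control sites will receive the full intervention after 1 year when the first set of comparison with the intervention site has been completed". Tele-health, the call centre, training and community awareness are shared by both groups: they "will be key cross cutting interventions, implying they will benefit the intervention site as well as control site". What the controls wait a year for is the equipped newborn unit.

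**Discussion (measuring results).** Change is judged against baseline benchmarks. One sentence undertakes to count only results attributable to the intervention, because "there are many other efforts towards improving the helthcare of newborns in the target area". It names no method for separating the two.

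**The concern.** The design section sets up a comparison group in order to assess effects, and equipped units at four hospitals are delayed by a year so that a first comparison can be made. The primary outcome then adds those four hospitals to the other five on both sides of a before-after comparison. Nothing in that measure removes change over calendar time.

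The primary result therefore cannot separate the project from whatever else changed in the county. A fall produced by other programmes would read as project success, and a background rise would hide a real benefit. This would be so even with perfect recording of deaths.

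**Working it through.** The document gives no expected number of deaths, power or trend for the primary outcome, so there is no figure of its own to reproduce. The check is of what the stated measure returns.

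**Inputs from the document**
- Nine hospitals counted, made up of five implementation and four control (Primary outcome measure; Study design; Selection of hospitals for the study).
- Controls receive the full intervention after 1 year (Study design).
- Period October 2015 to December 2018: 3 months in 2015 plus 36 months = 39 months.

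**Assumptions**
- Annual background change: not given; 3% and 5% are used as a range.
- Length and position of the earlier period: not defined; adjacent windows of 39 and of 12 months are used.
- Births and facility use constant, so that a trend in mortality carries over to the count.

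**Formula.** Let b be the proportional background fall between the two periods and e the true project effect.
- Before-after measure: 1 − (1 − b)(1 − e).
- Relative to concurrent controls with the same b: 1 − [(1 − b)(1 − e)]/(1 − b) = e.

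With e = 0 the before-after measure returns b in full. With b = 20% and e = 10% it returns 1 − 0.80 × 0.90 = 28%, where the controlled contrast returns 10% under parallel trends.

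**Annual trends.** Adjacent windows of equal length have midpoints one window apart: 39/12 = 3.25 years, or 1 year for 12-month windows. For an annual decline r, b = 1 − (1 − r)^gap.

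| Assumed decline per year | Apparent reduction, 39-month windows, e = 0 | Apparent reduction, 12-month windows, e = 0 |
|---|---|---|
| 3% | 1 − 0.97^3.25 = 9.4% | 3% |
| 5% | 1 − 0.95^3.25 = 15.4% | 5% |

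**The other direction.** Take a background rise of 3% a year and a true effect of 10%. Over 39-month windows the measure shows 1 − 1.03^3.25 × 0.90 = 1 − 1.101 × 0.90 = 0.9%. Over 12-month windows it shows 1 − 1.03 × 0.90 = 7.3%.

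**Does aggregation by facility help?** A before-after percentage for each hospital still contains that hospital's background change, and no step contrasts the five with the four. Even if the results were grouped afterwards, the controls would have had the full intervention for 39 − 12 = 27 of the 39 months, if crossover came 12 months after October 2015. The whole-period figure would not be a clean contrast.

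**The case against.** **The protocol does plan a controlled comparison.** This stands. A reader might infer that the study has no control analysis at all, and the text does not support that: the Abstract and Study design both describe a comparison group, and a first comparison is due at 1 year. What is missing is the link. Study design does not say that this comparison concerns deaths, and the Primary outcome measure section describes a different one.

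**The analysis may be specified elsewhere.** An outcome definition and its analysis are often written separately, and an analysis plan may exist. Here, however, the article does not defer the comparison. It states which counts are set against which, and an analysis using the controls would depart from that statement.

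**The Discussion promises attributable results only.** It does, and the intent deserves credit. But it gives no method, and the concurrent controls, the one stated design feature that could deliver it, are not used as such in the primary outcome.

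**The size is hypothetical.** This stands. A reader might infer that background trend alone would meet the 30% target in the Abstract. That would take about 10.4% a year over 39-month windows (1 − 0.70^(1/3.25)) or 30% a year over 12-month windows, and nothing in the document supports either. Nor must the bias favour the project. The outcome is a count, and the project hopes to raise presentation of neonates with complications from 21% to 32%. If fatality among those presenting fell by 30%, deaths among them would still change by 32/21 × 0.70 = 1.067, a rise of 6.7%.

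**The controls are imperfect.** This stands and shapes the fix. Sites are chosen purposely, the two hospitals with some neonatal facilities are placed among the intervention sites, and the Study assumption section concedes that the groups may not be comparable.

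**Conclusion.** The point holds as a conflict between the design and the primary outcome. The design provides a concurrent comparison, while the primary outcome is a pooled before-after change in which the controls are counted but never compared. Background change, plausible given the concurrent efforts that the Discussion describes, is attributed to the project in full and in either direction.

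The size cannot be fixed from the document. Under an assumed 3% to 5% annual decline, no project effect and constant births and facility use, the apparent reduction is 9% to 15% with adjacent 39-month windows and 3% to 5% with 12-month windows. These are illustrations of the mechanism. The mechanism itself needs no trend assumption: the measure has no term for background change.

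**What to change.** In the Primary outcome measure section:

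1. Base the effect estimate on the change in newborn deaths at the five implementation hospitals relative to the concurrent change at the four controls. Use the first year, before the controls cross over, and the matching pre-intervention months, with facility and calendar-time effects.
2. Define exposure as receipt of the project's refurbished or equipped unit. Merely having a unit will not serve, because two intervention hospitals already had some neonatal facilities.
3. Use births or admissions as the denominator where they are recorded, since raw counts also move with facility use.
4. State the length and dates of the earlier period.
5. Keep the nine-hospital before-after percentage, worded as descriptive change over the period and not as a project effect.

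**Costs to state openly**
- A wider interval, with only nine hospitals and a one-year contrast.
- Reliance on parallel trends between purposely selected sites.
- An estimate limited to the equipped units, because the other components reach the controls too. It does not test the whole package named in the Hypothesis section.
- Possible retrospective abstraction of earlier counts by facility. The article describes abstraction throughout the project period and does not show that a monthly series before October 2015 exists.
- A documented change to the primary effect in a study that has already commenced and is registered.

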### Secondary outcome measures

Percentage of mothers or care givers able to identify at least three danger signs in neonates in the project area; **Numerator**: Number of mothers/ care givers who can identify at least three danger signs in neonates in the project area**. Denominator**: Sampled mothers/care givers in selected community areas at baseline and end line.Proportion of neonates with complications referred to specialized neonatal units, through the call center; **Numerator**: Number of neonates with complications referred to specialized neonatal centers, through the call center. **Denominator**: Total number of neonates reached through the call center.Percentage of health providers in neonatal care units who adhere to expected neonatal standards of care (rapid and complete application of standard protocols); **Numerator**: Number of health workers in neonatal care who adhere to expected standards of neonatal care in the nine selected facilities. **Denominator**: Total number of health workers in neonatal care in the selected facilities.Percentage increase in neonates with severe complications in the specialized neonatal units; Percentage change in the number of admissions of neonates classified as having severe complications (using the 15-score index) over the project period.Percentage of neonates who stay in NBU beyond 5 days; **Numerator**: Number of neonates who stay beyond 5 days. **Denominator**: Total number of neonates admitted in the 9 specialized neonatal units

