### Sample size determination

#### Selection of community members (newborn mothers)

Bungoma County, the area targeted by community sensitization will be source area for target newborn caregivers/newborn mothers who will be simple randomly selected to participate in the survey. Statistical methods for determining sample size will be employed to ensure the correct sample size is picked to avoid biases and ensure the outcomes are valid. There are approximately 29,845 births in Bungoma County per annum [16]. This number will be split twice for control and intervention group. The study will allow a margin of error of 5% at confidence level of 95% to obtain the correct sample size for the study. It is also expected that at least one of the variables of interest (e.g., knowledge of 3 danger signs in neonates) will be 50% among the respondents. Using the formula:$$ x=Z{\left({}^c{/}_{100}\right)}^2r\left(100-r\right) $$$$ n{=}^{N\ x}{{/_{\Big(\left(N-1\right)E}}^2}_{+x\Big)} $$$$ E=\mathrm{Sqrt}\left[{}^{\left(N-n\right)x}{/}_{n\left(N-1\right)}\right] $$where *N* is the population size, *r* is the fraction of responses that we are interested in, and *Z*(*c*/100) is the critical value for the confidence level *c*, we get 375 as our ideal sample size in the control and intervention areas (i.e., four data collectors in each area conducting 8 surveys daily for 12 working days each). See Additional file 1.

**Table 1 Tab1:** Outcomes and objectives

Outcomes	• Increased access and utilization of quality neonatal care services. • Health system management strengthened to deliver quality neonatal health services.
Objectives	i) To setup 7 differentiated neonatal special care units in 7 sub-county hospitals in Bungoma. ii) To train 90 selected health workers (nurses and clinicians) based in 9 sub county hospitals in neonatal care to be able to diagnose and manage common new-born problems and make timely referral when appropriate. iii) Establishing a tele-health platform that will ease diagnostic and new-born clinical care consultant support iv) Re-packaging and distribution of best-practice clinical guidelines into user friendly formats. v) Develop a mobile phone based follow up system for all new-borns for early detection of neonatal problems and initiation of appropriate action.

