### Quantitative data

Questionnaires –
i.This will be administered to health workers to check their knowledge, attitudes and practices in neonatal care.ii.Community (mothers of newborns/caregivers) to assess effect of information on their knowledge of danger signs and utilization of neonatal services.
Check list – Will consist of a list of equipment available in the new born care unit, their condition, and frequency of useData abstraction form –This will be developed to collect routine health facility records in the neonatal unit to ensure completeness and accuracy in data generated. The trained nurses and clinical officers will ensure correct data entry which will be monitored periodically by the hospital facility in conjunction with the project. The trained staff will also mentor other staff in the facility (OJT) to also develop competency and correct data recording and entry.Client exit interviews –will be administered to clients from new born unit to capture the perception of clients on quality of care provided, and the outcome of the service.

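### Secondary outcome (a) cuts the number of danger signs identified at three; adding an analysis of the number itself would usually detect a moderate, general gain in knowledge better, at little cost

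*Protocol article*

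**What the plan says.** Secondary outcome measures defines outcome (a) as a percentage. The numerator is the "Number of mothers/ care givers who can identify at least three danger signs in neonates in the project area" and the denominator is "Sampled mothers/care givers in selected community areas at baseline and end line".

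Selection of community members (newborn mothers) sizes the survey by precision: "The study will allow a margin of error of 5% at confidence level of 95% to obtain the correct sample size for the study". It expects that "at least one of the variables of interest (e.g., knowledge of 3 danger signs in neonates) will be 50% among the respondents" and arrives at 375 for the control and intervention areas, with mothers chosen by simple random sampling.

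The Quantitative data section says the questionnaire for mothers and caregivers is meant "to assess effect of information on their knowledge of danger signs and utilization of neonatal services".

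The Study design and Control group sections say that community awareness work reaches control sites as well as intervention sites.

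For outcome (a), the article gives no target change, power, test or distribution of the number of signs. It does not say that the number is discarded.

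**The concern.** Whether a mother reaches three signs cannot be scored without counting the signs she identifies. The survey therefore produces a graded measure (0, 1, 2, 3 and so on), and the only outcome defined on it is the share at or above three. A shift in the population from no signs to two, or from three to six, leaves that share unchanged, although the questionnaire is meant to show the effect of information on knowledge.

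On the article's illustrative 50%, the cut sits near the median. If the number were roughly normal, cutting it there would keep about 2/π, or 64%, of the information about a general shift. At stake is the chance of detecting a moderate gain in knowledge with the same mothers and the same questions.

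**Working it through.** **Inputs from the article.** "There are approximately 29,845 births in Bungoma County per annum"; "This number will be split twice for control and intervention group"; 50% expected; margin of error 5 points; 95% confidence; 375 per area.

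**Inputs assumed here.** True changes of 2 to 20 percentage points, two-sided 5% tests, independent simple random samples of 375 on each side of the comparison, and a shift of the whole distribution unless stated otherwise.

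**Step 1: reproduce the 375.** N = 29,845/2 = 14,922.5, and x = 1.96² × 50 × 50 = 9,604. Then n = N·x/((N − 1)·5² + x) = 14,922.5 × 9,604/(14,921.5 × 25 + 9,604) = 374.5, rounded up to 375. The figure holds. The stated workload agrees with a per-area reading: 4 collectors × 8 surveys × 12 days = 384.

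**Step 2: power of the yes/no outcome.** With p̄ the average of the two proportions, power = Φ[(Δ − 1.96·√(2p̄(1 − p̄)/n)) / √((p₁(1 − p₁) + p₂(1 − p₂))/n)].

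For 50% to 58%: √(2 × 0.54 × 0.46/375) = 0.03640 and √((0.25 + 0.2436)/375) = 0.03628. So (0.08 − 1.96 × 0.03640)/0.03628 ≈ 0.239, and Φ = 0.594.

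**Step 3: power of the uncut measure for the same change.**

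- Normal score: shift d = Φ⁻¹(0.58) − Φ⁻¹(0.50) = 0.202. Then d·√(375/2) − 1.96 ≈ 0.804, and power is 0.789.
- Poisson count: the means giving 50% and 58% at three or more are 2.67 and 3.01. Then 0.34/√((2.67 + 3.01)/375) − 1.96 ≈ 0.803, and power is 0.789.

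**Step 4: repeat over a range of true changes from 50%.** Losses are taken from unrounded values.

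| Change (points) | Yes/no | Normal score | Loss (points) | Poisson count | Loss (points) |
|---|---|---|---|---|---|
| 2 | 7.9% | 10.1% | 2.3 | not run | – |
| 5 | 27.8% | 40.5% | 12.8 | 40.3% | 12.5 |
| 8 | 59.4% | 78.9% | 19.5 | 78.9% | 19.4 |
| 10 | 78.7% | 93.4% | 14.7 | 93.5% | 14.8 |
| 11 | 85.9% | 96.9% | 11.0 | 97.0% | 11.0 |
| 12 | 91.3% | 98.7% | 7.4 | 98.7% | 7.4 |
| 15 | 98.7% | about 100% | 1.3 | about 100% | 1.3 |
| 20 | about 100% | about 100% | 0 | about 100% | 0 |

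**Step 5: other count distributions, changes of 5 to 11 points.** A binomial count on 5 signs gives losses of 9 to 15 points. A negative binomial with size 3 gives 12 to 24.

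**Step 6: other contrasts (normal score).** With both areas pooled, 750 v 750, the loss is 19 points for a 5-point change but 2 for a 10-point change. A difference-in-differences with 375 per area per survey gives 7 points for a 5-point change, 19 for 10, 13 for 15 and 2 for 20.

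**Step 7: a shift confined to the cut.** Take the Poisson baseline (mean 2.67) and move 10% of mothers from two signs to three, with no other change. The mean rises by only 0.10. The yes/no outcome has 78.7% power and the mean count has 13.2%. The advantage reverses.

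**The case against.** The strongest objection is that the size of the loss depends on figures the article does not supply. A reader might infer that this survey gives up 10 to 19 points of power whatever happens. The documents do not support that. The range belongs to changes of about 5 to 11 points under a general shift, and the loss all but vanishes at 15 points. The nearest stated target, health workers' knowledge rising from about 65% to 90%, concerns another group, but it shows that a small change is not the article's own assumption. The reversal in Step 7 is also real: a campaign that teaches a short list of signs could move mothers mainly across the cut. All of this stands, and it is why the point is worded conditionally.

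A reader might also infer that the survey is too small because of the cut. It was sized for a 5-point margin on a percentage, and the cut leaves that precision as it is. A test for this outcome may properly be left to an analysis plan that is not shown.

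It is tempting to say that half the mothers start above the cut and cannot show a gain. That treats the survey as a cohort. The article describes random selection of newborn mothers and nowhere says that the same women are re-interviewed. The 50% is itself a sizing value for at least one variable, with this outcome as the example. Nor is a rise in knowledge the first study question as such, since that question asks how knowledge and service availability affect use of hospital services.

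Finally, recording the number of signs is compatible with the text, and the questionnaire may already do so. What survives is narrower: the one outcome defined on the questionnaire's danger-sign item uses only part of what the interview must obtain.

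**Conclusion.** The point holds as a minor, conditional inefficiency. It is not an error or a contradiction. With 375 on each side, 50% at the cut, a general shift and a true change of about 5 to 11 percentage points, the yes/no outcome has roughly 10 to 19 points less power than a comparison of the number of signs. Less favourable or more dispersed count models widen that to about 9 to 24. Outside that band the loss is small, and if the effect is concentrated between two and three signs the yes/no outcome is the stronger one.

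Because awareness work reaches both areas, baseline against end line is the more natural lead contrast for knowledge than one area against the other. That is an inference from the design, since the article names no test. The possible reversal is also the reason to keep the percentage rather than replace it.

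**What to change.** In Secondary outcome measures, state that the number of danger signs correctly identified is recorded for each mother or caregiver. Add a prespecified analysis of that number: a count or ordinal model, or a mean difference with robust standard errors. Lead with the change from baseline to end line, and report it by area as well. Keep the percentage identifying at least three signs as the defined indicator, with its present numerator and denominator.

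The cost is one extra analysis, on a scale less familiar to programme readers than a percentage. No extra mothers, visits or questions are needed. One limit applies: the study has already commenced, so the comparison with baseline is possible only if the baseline forms recorded the number and not just whether three was reached. That should be checked first. If they did not, the number can still be compared between areas at end line, with the caution that both areas will have had the awareness work.

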### Control group – Minimizing bias and contamination

To minimize bias and contamination, the intervention sites will be selected purposely from the nine county and sub- county hospitals. The sites selected will include the two facilities that have some level of neonatal facilities to ensure that the intervention sites and the control sites have distinct features separating the two.

We will measure the utilization of services in the selected facilities at baseline, mid-term and end-line levels.

To determine utilization of neonatal services, we will collect data directly from the source through a data abstraction form in the nine health facilities throughout the project period. Further, the community health workers and volunteers will also provide information of the number of cases they refer to specific facilities. Cases that fail to arrive at the health facilities will also be captured and the data from the facilities and the community health workers will be cleaned, cross checked and analyzed to provide required results for utilization of neonatal services.

Quality of care will be determined through observations of service provision by clinicians, as well as checking use of neonatal equipment and the severity of conditions managed by the health providers in the units.

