#### Rationale

The project will establish 7 new special care units and enhance capacity in 2. Following the 3 months module based competency based neonatology course for 90 health care workers in these units, it will be important to provide medical consultation support by pediatricians. This will facilitate timely clinical decision making including and not limited to; judicious use of medicines such as antibiotics, change of treatment, fluids administration, nutritional calculations, immunization decisions, evolution of diagnosis, need for referral and follow up strategies. This virtual support will build the clinicians confidence in clinical management of newborns, knowing that they can ask and get help at any time of the day, all week, ultimately improving outcomes.A major challenge for clinicians working in peripheral, rural areas in Kenya, has been keeping in touch with best care practices due to inability to access this information, lack of continuous education on how to apply the updates on best care and failure of follow up on adoption of best care practices. The telehealth platform will provide virtual best care practices updates service regularly and interactively. Pediatricians and the special units’ clinicians will be able to discuss on implementation of the updates, challenges they face and lessons learnt. This will promote free flow of information between the consultants and the clinicians, promoting best care practices and newborn outcomes.The telehealth platform will enable data collection on clinical challenges and gaps that will inform project evaluation, areas of emphasis in the continuous medical education and enhanced efficiencies in other processes such as call center follow up and referral systems.

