#### Control group

The study ensures that the control group will also receive the full intervention towards the end of the project period so that they do not remain disadvantaged. Initially they shall benefit from community sensitization, tele health platform and call center. After a period of 1 year, the control group will be ready for the full intervention which will include establishment of functional specialized neonatal units.

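### Stay beyond 5 days is scored only in nine specialized units, seven of which the project itself creates, so as written it has no control value in year 1 and no baseline at seven hospitals

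*Protocol article*

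**What the plan says.** The protocol article (Secondary outcome measures) labels the last secondary outcome as the percentage of neonates staying in the NBU beyond 5 days. Its numerator is "Number of neonates who stay beyond 5 days" and its denominator is "Total number of neonates admitted in the 9 specialized neonatal units". No period, arm or fixed set of units is attached.

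Other sections say when those units come into being:

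- Telehealth platform, Rationale: "The project will establish 7 new special care units and enhance capacity in 2". Anticipated impact and Table 1 also describe seven units to be set up.
- Study design: "Five hospitals will be the implementation sites while 4 hospitals will be control sites in a step wedge approach".
- Study design, on timing: "The control sites will not receive the main intervention benefits (equipped specialized newborn units) until after 1 year of implementation in the experimental sites". The same section has the controls cross over once a first comparison with the intervention sites is complete.
- Control group: after a year the controls receive "the full intervention which will include establishment of functional specialized neonatal units".
- Control group – Minimizing bias and contamination, on choosing the intervention hospitals: "The sites selected will include the two facilities that have some level of neonatal facilities".

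**The concern.** The Study design section includes a comparison group so that intervention effects can be assessed, and says indicators will be measured within each site at different time points. An outcome can serve those purposes only if it can be scored in both arms and in each period. Outcome (e) is tied to a structure that is itself the main intervention. A sick newborn cared for elsewhere in a control hospital during year 1 falls outside both numerator and denominator.

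Two things are at stake. The year-1 contrast between arms has nothing on the control side for this outcome. And an overall percentage over whichever units are open would compare different sets of hospitals at different times, so it could change with no change in length of stay anywhere.

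**Working it through.** **Unit count.** The denominator names 9 units. The telehealth Rationale gives 7 new + 2 enhanced = 9, so the figure is reproduced. It is reached only when every new unit has opened.

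**Split by arm.** There are 5 intervention and 4 control hospitals. If the 2 existing units are both intervention sites (the natural reading of the section on minimizing bias), new units in the intervention arm = 5 − 2 = 3 and in the control arm = 7 − 3 = 4. That agrees with the Study design section, under which no control hospital has an equipped unit during year 1.

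| Period | Intervention units | Control units | Total |
|---|---|---|---|
| Baseline | 2 of 5 | 0 of 4 | 2 |
| Year 1, intervention units open | 5 of 5 | 0 of 4 | 5 |
| After the controls cross over | 5 of 5 | 4 of 4 | 9 |

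**Consequences under the literal denominator.**
- Year 1: the control percentage is 0/0. Hospitals without a value: 4/9 = 44%, which is the whole control arm.
- Baseline: 9 − 2 = 7 hospitals have no value, including 3 of the 5 intervention hospitals.

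**Could a pooled percentage move by composition alone?** The article gives no length-of-stay figures, so the rates here are assumptions. Let existing units have rate a, new units rate b, and let each existing unit have w times the volume of a new one. With k new units open and no change inside any unit:

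pooled = (2·w·a + k·b) / (2·w + k), for k = 0, 3, 7.

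- a = 40%, b = 20%, w = 1: 40%; (80 + 60)/5 = 28%; (80 + 140)/9 = 24.4%. Shift −15.6 points.
- a = 20%, b = 40%, w = 1: 20%; (40 + 120)/5 = 32%; (40 + 280)/9 = 35.6%. Shift +15.6 points.
- a = 40%, b = 20%, w = 3: 40%; (240 + 60)/9 = 33.3%; (240 + 140)/13 = 29.2%. Shift −10.8 points.
- a = 20%, b = 40%, w = 3: 20%; (120 + 120)/9 = 26.7%; (120 + 280)/13 = 30.8%. Shift +10.8 points.
- a = b: no shift.

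The pooled figure can therefore rise, fall or stay put, depending on rates and volumes that the document does not give.

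**Contrast within the article.** The primary outcome counts deaths at the nine project facilities, and provider adherence also refers to nine selected facilities. A facility-based definition is thus already used elsewhere; (e) departs from it.

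**The case against.** The strongest reply is that control hospitals may have had a newborn area all along. The label of (e) uses the broader term NBU, the interview list includes nine staff in charge of newborn units, and the abstraction form is described as covering neonatal-unit records. The Abstract says only two hospitals are fairly equipped, not that the other seven have nothing. This stands in part: a reader might infer that control hospitals admit no newborns anywhere that could be counted, and the documents do not establish that. The empty control cell follows from the denominator as written, which names specialized units. If basic areas are meant to count, the definition needs to say so.

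Second, no sentence assigns (e) to the year-1 comparison, and (e) is a plain percentage with no stated before/after contrast. The choice of outcomes to compare by arm can properly be left to an analysis plan. That also stands: it cannot be said that a planned analysis of (e) fails. But the comparison group is there to assess intervention effects and no outcome is exempted, while the denominator is fixed in this document.

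Three stronger readings are tempting and not supported:
- That the only between-arm comparison is lost. The article speaks of a first set of comparisons, which implies others.
- That the pooled value will shift. It only could.
- That the exit interviews, which "will be administered to clients from new born unit to capture the perception of clients on quality of care provided", undermine an outcome in the same way. Client-rated quality is not among the listed outcomes, and quality of care is to be judged by observation, equipment use and severity of the conditions managed.

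Finally, widening (e) to every ward would change what it measures, because maternity stays may be determined by the mother. That is right, and it limits the fix.

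**Conclusion.** The point holds as a defect in how one secondary outcome is defined. Taken literally, (e) has no control value in year 1 (0 of 4 control hospitals) and no baseline at 7 of 9 hospitals. Any value pooled over open units rests on 2, then 5, then 9 hospitals and may move through that alone.

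The conclusion assumes that the specialized units in the denominator are the units the project sets up or enhances. The 2-5-9 sequence also assumes that both existing units are intervention sites; the absence of control units in year 1 rests directly on the Study design section. The size and direction of any pooled shift are unknown, and the shift is nil if existing and new units share the same rate. The primary outcome is not affected, and no power claim is attached to (e). The definition should be changed, but this does not threaten the study as a whole.

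**What to change.** Define the denominator of (e) as neonates admitted for illness or complications to the newborn unit, or to the ward that serves that purpose before the unit opens, at each of the nine hospitals. Use the same denominator for the numerator's stays beyond 5 days. Abstract both the same way in every period, and report them by arm and as change within the same hospital, not pooled over whichever units are open. Restricting to illness or complications keeps well babies on maternity wards out of the measure.

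If only unit stays can be abstracted, state that (e) is a descriptive indicator by hospital from the opening of each unit, and draw no between-arm or pooled before/after conclusion from it.

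The cost is a change of wording and some extra register abstraction at hospitals without a unit. Abstraction is already planned at all nine facilities throughout the project, although the article does not show that ward registers record neonatal length of stay, so this should be checked first. Some change in case mix when a unit opens will remain and should be acknowledged when (e) is interpreted.
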